#### Primary outcome

2.12.2

The number of CSBM per week is the primary outcome. It is effective when the number before the intervention subtracted from the number after the intervention is more or equal to 1.

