#### Baseline information

2.12.1

Baseline information will include demographic data and clinical data from the participants after allocation. Demographic data includes gender, age, height, weight, nationality, occupation, and education level. Clinical data includes past medical history, drug allergy history, the history of medications used to treat or induce constipation, dietary habits in the past year (see Supplementary Table 3),^[21]^ the primary outcome and secondary outcomes.

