### Planned statistical analysis

2.15

Continuous variables will be described as the mean ± standard deviation (SD), median or interquartile range (IQR). The number of cases, frequency, the rate and the constituent ratio will be described by categorical variables. Variance analysis will be used for continuous variables in the baseline data having normal distribution and same variance. Wilcoxon rank sum test or Kruskal–Wallis *H* test will be used for the comparison of differences between groups that are not normally distributed or have uneven variance. Categorical variables will be tested by chi–square test or Fisher exact test. Wilcoxon rank sum test or Kruskal–Wallis *H* test will be used for the number of CSBM per week in primary outcome. Chi–square test or Fisher exact test will be used for percent improvement of each symptom scale score in secondary outcome indicators. The result of 48-h GITT will be analyzed using chi-square or Fisher test. Wilcoxon rank sum test or Kruskal–Wallis *H* test will be used for measurement data in HRAM, while chi-square test or Fisher exact test will be used for counting data. Safety, dietary quality, compliance indicators will be tested by chi-square test or Fisher exact test. Wilcoxon rank sum test or Kruskal–Wallis *H* test will be used to compare the diversity, the relative abundance of bacteria in phylum and genera level between 2 or more groups.^[22]^ Complying with the intent-to-treat (ITT) and per-protocol (PP) principle, all data of the patients randomized and at least 1 assessment (include baseline assessment) will be analyzed. For dropouts and terminations, their missing data will be obtained by last-observation-carried-forward (LOCF) method. All statistical analyses will be performed by SPSS20 software (IBM, Chicago, Illinois), and *P* value <.05 will be considered statistically significant.

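### The primary test leaves out the baseline CSBM count that the trial collects, and the analysis section does not fix whether follow-up value or change is compared, or at which visit

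*Protocol article*

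**What the plan says.** Section 2.12.2 (Primary outcome) has two sentences. The first names the variable: "The number of CSBM per week is the primary outcome". The second sets a rule for calling the treatment effective in a patient: "It is effective when the number before the intervention subtracted from the number after the intervention is more or equal to 1". That rule is a gain from baseline of at least 1 CSBM per week.

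Section 2.15 (Planned statistical analysis) assigns the test: "Wilcoxon rank sum test or Kruskal–Wallis *H* test will be used for the number of CSBM per week in primary outcome". Change, baseline value and visit are not mentioned there. For the secondary symptom scales, section 2.15 does name a test for the response categories: "Chi–square test or Fisher exact test will be used for percent improvement of each symptom scale score in secondary outcome indicators". A general sentence also says "Categorical variables will be tested by chi–square test or Fisher exact test".

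Section 2.12.1 (Baseline information) lists among the data collected "dietary habits in the past year (see Supplementary Table 3),^[21]^ the primary outcome and secondary outcomes", so a baseline CSBM value will exist for each patient. For baseline data, section 2.15 names only comparisons between groups: "Variance analysis will be used for continuous variables in the baseline data having normal distribution and same variance". Section 2.2 has outcomes assessed at baseline, day 14 and day 28. Section 2.6 gives 23 participants per arm in each subtype.

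**The concern.** The outcome section and the analysis section do not meet. The first judges success by each patient's change from baseline. The second compares groups on the number alone. Three things follow.

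- **The primary variable is not fully fixed.** The number could be the follow-up value or the change, at day 14 or at day 28. A count and a responder rate both stand under the primary outcome heading. In an eight-arm programme (two subtypes, four arms each), that leaves room to choose after the data are seen.
- **Baseline is measured but not used in the primary comparison.** Any variation between patients that baseline would explain stays in the error term. Testing the arms for baseline differences does not recover it.
- **No test is named for the success rule**, although one is named for the comparable categories on the secondary scales.

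At 23 per arm, the second of these costs the most information.

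**Working it through.** **The document's own figure.** The only stated sample-size figure is 92 per subtype: 4 × 23 = 92, which reproduces. No effect size, SD, power or baseline-outcome correlation is given, so there is no power figure to reproduce.

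**Inputs.** From the article: n = 23 per arm and a significance level of 0.05. Assumed: a two-sided test, equal SD at baseline and follow-up, a baseline-outcome correlation r of 0.3, 0.5 or 0.7, and a true difference of d = 0.6 SD between two arms.

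**Step 1: variance.** The variance of a baseline-adjusted difference, relative to a comparison of follow-up values, is 1 − r². The equivalent gain in sample size is 1/(1 − r²).

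| r | 1 − r² | variance cut | 1/(1 − r²) |
|---|---|---|---|
| 0.3 | 0.91 | 9% | 1.10 |
| 0.5 | 0.75 | 25% | 1.33 |
| 0.7 | 0.51 | 49% | 1.96 |

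**Step 2: power, 23 vs 23.** This uses the non-central t distribution with 44 degrees of freedom and non-centrality d/√(1 − r²) × √(23/2).

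| Analysis | non-centrality | power |
|---|---|---|
| Follow-up value only | 0.6 × 3.391 = 2.03 | 51% |
| Adjusted, r = 0.3 | 2.03/√0.91 = 2.13 | 55% |
| Adjusted, r = 0.5 | 2.03/√0.75 = 2.35 | 63% |
| Adjusted, r = 0.7 | 2.03/√0.51 = 2.85 | 80% |

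Taking off one degree of freedom for the covariate changes none of these rounded figures.

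**Step 3: the tests compared directly.** Step 2 is a t-test approximation, whereas the plan names rank tests. A simulation therefore compared the candidate analyses: 4,000 runs, normal data, 23 vs 23, with assumed SD 1.5, difference 1 CSBM per week and control gain 0.5.

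| r | Wilcoxon, follow-up value | Wilcoxon, change | ANCOVA | Chi-square, gain ≥ 1 |
|---|---|---|---|---|
| 0.2 | 58% | 39% | 62% | 31% |
| 0.3 | 57% | 44% | 64% | 34% |
| 0.5 | 56% | 57% | 72% | 44% |
| 0.7 | 57% | 78% | 86% | 63% |

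ANCOVA has the highest power in every row. An unadjusted change score has relative variance 2(1 − r), so it beats the follow-up value only when r exceeds 0.5. The responder test is weaker than the planned rank test at r = 0.2 to 0.5 and slightly stronger at 0.7. The precision loss therefore comes from leaving baseline out, and making the success rule the primary test would usually make matters worse.

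**The case against.** Several stronger readings are tempting, and the documents do not support them.

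- **That the primary outcome is the gain of at least 1.** It is not. Section 2.12.2 names the number of CSBM per week first, and the test in section 2.15 addresses that variable. The gain is an added rule.
- **That the success rule will never be tested.** This goes too far. A yes/no rule is categorical, and the general sentence on categorical variables could cover it. That sentence follows the ones on baseline data and non-normal group comparisons, so its scope is unclear. What can be said is that no test is tied to the rule.
- **That the article states an analysis of raw follow-up values.** It says only the number. The follow-up value is the natural reading, but change is not excluded.
- **That baseline is used for nothing but significance tests.** The success rule itself is computed from it.

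The defence goes further. An unadjusted rank comparison of randomised arms is valid, and its type I error already allows for chance imbalance. A chance baseline difference carries into a follow-up comparison only in proportion to r, about 30% of it at r = 0.3. Covariates are often left to a fuller plan. The trial is declared exploratory, and the Discussion defers verification to a larger trial. The success rule also refers to the number after the intervention, which points towards the end of treatment.

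Most of this stands and limits the severity. It does not remove the point. The article does not leave the primary test open: it names one, and that test omits a measurement already in hand. The sentence naming it also leaves variable and visit undefined.

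**Conclusion.** The point holds as a matter of efficiency and definition, not of validity. The primary test is fixed without baseline. The variable it compares is not fixed as follow-up value or change, or as day 14 or day 28. The success rule has no assigned test.

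The size of the precision loss rests on assumptions, because the article gives no correlation, SD or effect size. For r between 0.3 and 0.7, adjustment is worth 10% to 96% more patients. At d = 0.6, power rises by between 4 percentage points (r = 0.3) and 29 (r = 0.7). At the low end the gain is small; its direction is not in doubt if baseline and follow-up correlate more than trivially. These figures describe one two-arm comparison, not the four-arm Kruskal–Wallis test. The plan should be changed on this point, but the flaw does not invalidate the trial.

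**What to change.** In section 2.12.2, state one primary variable: CSBM per week at the day-28 assessment, with the diary days it averages. In section 2.15, replace the primary test with an analysis of that variable with baseline CSBM per week as covariate (ANCOVA, or rank ANCOVA if the counts are skewed). Report the adjusted difference with its 95% confidence interval.

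Keep the gain of at least 1 CSBM per week as a named secondary responder analysis, using chi-square or Fisher with a risk difference, and not as the primary test. The baseline significance tests can be dropped, since they do not affect the primary result.

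One condition applies. Section 2.12.1 places baseline collection after allocation, and patients know their diet assignment. The covariate should be recorded before the assignment is revealed.

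The cost is a few sentences in sections 2.12.1, 2.12.2 and 2.15, agreed before unblinding. No new measurement and no extra patients are needed.

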#### Secondary outcomes

2.12.3

*CSS:* The scale for constipation-related symptoms is used for investigating the degree and frequency of symptoms mentioned in Roman IV diagnostic criteria for FC. The degree of discomfort is assessed by visual analog scale (VAS), in which 0 represents no discomfort and 10 represents very strong discomfort. The final scores are obtained with the multiplication of the 2 and then divided by the average number of defecations per week (see Supplementary Table 4). Percent improvement will be calculated as following:
 

Recovery means symptoms disappeared; Marked improvement means percent improvement is more than or equal to 80%; Progress means percent improvement is more than or equal to 50% but less than 80%; Ineffective means percent improvement is less than 50%.

*TCMSS:* The TCMSS is established by collecting information about effects of relevant syndromes of TCM constipation, which are assigned 0, 1, 2, and 3 points representing normal, mild, moderate, and severe degrees, respectively. Normal refers to the absence of this syndrome, mild refers to a slight impact on life, moderate means a significant impact on life and severe refers to the serious impact on life (see Supplementary Table 5). Nimodipine method is used for evaluating the effects of relevant syndromes of TCM constipation.
 

Symptoms, signs disappeared or basically disappeared and syndrome integral reduced more than or equal to 95% is considered clinical cure; Significantly effective means that symptoms, signs significantly have improved and syndrome integral has reduced more than or equal to 70%; Effective means that symptoms, signs have improved and syndrome integral have reduced more than or equal to 30%; Ineffective means that symptoms, signs have no improved or have even aggravated and syndrome score has reduced less than 30%.

*48-h GITT:* 48-h GITT is a simple method for evaluating the function of gastrointestinal motility. The barium residue rate is the ratio of the number of barium remaining in the body 48 hours after swallowing 20 barium bars with a standard meal. Higher residue rate indicates the worse gastrointestinal transport function. The parameters include barium excretion rate after 48-hour, residue rate above rectosigmoid colon and residue rate within rectosigmoid colon. The barium excretion rate in normal people is more than or equal to 90%.

*HRAM:* HRAM is used to estimate the function of anal sphincter, rectal sensation and anorectal reflex for diagnosing the defecation disorder constipation. The parameters include mean pressure of resting anal sphincter, maximum contraction pressure of resting anal sphincter, anal relaxation rate during analog defecation, first sensory value, defecation sensory value and maximum tolerance.

*FFD:* Fresh stools (<30 minutes, no drugs influencing on intestinal flora were taken in the past 2 weeks) from the participants are stored in a refrigerator at –80°C for flora detection. 16S rDNA sequencing is used to detect the distribution of fecal flora at the genus level.

#### Safety outcomes

2.12.4

Safety parameters include AEs and laboratory examinations (BR, LKF).

#### DQ and compliance measure

2.12.5

The number of qualified meals, total meals and the intake frequency of food involved will be calculated after getting the diary back. Diet high quality means a significant difference before and after intervention in diet groups, while there is no difference in non-diet groups. DCR means the ratio of qualified meals to total meals multiplied by 100. High compliance is achieved when DCR is more than or equal to 80%, while low DCR is less than 80%.

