### Study design

2.2

The protocol was drafted using the SPIRIT guidelines and the results will be reported following the checklist of the Consolidated Standards of Reporting Trials (CONSORT) statement (see Supplementary Table 1). All the participants will be informed about the study purpose and their signed informed consent will be obtained before joining this parallel-group study. A total of 92 participants will be recruited in each TFC or aTFC subtype following the inclusion and exclusion criteria. Then they will be allocated to drug + diet group, placebo + diet group, drug group and placebo group randomly at 1:1:1:1 ratio. The positive drugs are Macrogol 4000 Powder (Forlax, Beaufort Ipsen Industrie) and Chinese herb powder for TFC and aTFC groups respectively. Outcomes will be evaluated at baseline, the 14th day (followed-up by telephone) and 28th day by researchers blinded to the groups. Participants will be informed whether diet intervention is acted by the enrollment number and obtain the “drug” corresponding to the number, but they and the researchers will not know whether they are receiving a drug or a placebo. The whole study design is illustrated (see Fig. 1). A SPIRIT figure for the schedule of enrolment, interventions and assessments is also presented (see Fig. 2).

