### Sample size

2.6

Due to the lack of relevant evidence, this is an exploratory study with small sample size. A total of 92 participants for each subtype will be recruited and will be further divided in four sub-groups (23 participants in every sub-group).

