**Table 2 T2:**
[figure not shown]
The component of Chinese herb powder.

Patients with diet intervention should follow the above items and patients without diet intervention will continue their previous eating habits. The treatment period will last for 28 days. During the treatment period, patients will be required to keep a diary about diet and defecation. The diet diary will be designed with a semi-quantitative food frequency method, and the defecation diary will gather information about sensation, stool shape and duration of each defecation. On the 14th day, patients will be followed up via telephone to find out the situation during the treatment and count the average times of CSBM per week, the average scores of constipation symptoms and TCM syndrome in the first 14 days. After 28 days of treatment, a second follow-up will be carried out to understand situation of constipation (the same to the first follow-up) and to ask the patients to finish the examinations (48-hour GITT, HRAM, BR, LKF). Fecal flora of fresh stool (<30 minutes) from patients will also be reviewed and the diaries will be taken back. During the intervention, the patients will keep in touch with the researchers for queries about the treatment if any to control the exit rate and any other drugs that can relieve constipation are forbidden.

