### Quality control

2.11

Participants’ DQ will be assessed at the baseline and after the intervention. The foods involved are in LVD content.

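### The diet-quality rule sets a significant within-group change in the diet arms beside no difference in the non-diet arms, so it never compares the arms and reads non-significance as no change

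*Protocol article*

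**What the plan says.** Protocol article, DQ and compliance measure (2.12.5), gives the criterion: "Diet high quality means a significant difference before and after intervention in diet groups, while there is no difference in non-diet groups". The same section also defines a dietary compliance rate (DCR), the percentage of meals that qualify, with a cut at 80%. It has qualified meals, total meals and intake frequencies worked out from the returned diary.

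Quality control (2.11) gives the timing: "DQ will be assessed at the baseline and after the intervention". It adds that the foods concerned are those in the light vegetarian diet (LVD).

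Planned statistical analysis (2.15) names the test: "Safety, dietary quality, compliance indicators will be tested by chi-square test or Fisher exact test". It does not say whether the comparison is between arms or between time points. The threshold is a P "value <.05 will be considered statistically significant".

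Study design (2.2) allocates patients to "drug + diet group, placebo + diet group, drug group and placebo group randomly at 1:1:1:1 ratio". Sample size (2.6) states: "A total of 92 participants for each subtype will be recruited and will be further divided in four sub-groups (23 participants in every sub-group".

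Under Interventions (2.8), in the text after Table 2, "patients without diet intervention will continue their previous eating habits". The diary of diet and defecation kept during treatment is required of patients generally, not only of those on the diet.

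Baseline information (2.12.1) lists "dietary habits in the past year" among the clinical data and does not link it to DQ.

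**The concern.** The purpose of a diet-quality check is to show that the arms came to eat differently. That is a statement about the difference between arms, and the criterion never estimates it. One significant and one non-significant before-after test can arise when both sides changed by the same amount. Two significant tests can arise when the diet side changed far more than the control side.

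Three gaps in the wording add to this. The no-difference half has no margin, so its natural reading is failure to reach P below .05, which a small group achieves easily. The rule has no direction, so a significant move away from the diet in the diet arms would satisfy it. If the chi-square or Fisher test in 2.15 is meant for before against after, it treats two measurements on the same patients as independent.

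Some drift in the non-diet arms is plausible: those patients know their diet allocation and also keep a diet diary. At stake is whether the report labels the diet contrast correctly as delivered or not delivered.

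**Working it through.** **The plan's own figure.** 4 arms × 23 = 92 per subtype, which agrees with Sample size (2.6). The protocol gives no power, effect size or SD for diet quality, so there is nothing else to reproduce.

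**Inputs.**
- n = 23: one arm within a subtype (2.6).
- n = 46: two arms pooled within a subtype, 2 × 23.
- n = 92 per side: both subtypes pooled as well, 2 × 46.
- Alpha 0.05 (2.15), assumed two-sided because sidedness is not stated.
- d = mean change ÷ SD of change. All values of d are assumptions.
- A paired t-test stands in for the before-after test, with normal changes, equal SDs and independent sides. The protocol names chi-square or Fisher and does not define DQ as a continuous score, so the results show the logic of the rule rather than its exact error rates.

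**Formulas.**
- Within-group power π(d, n): noncentral t with n − 1 degrees of freedom and noncentrality d√n.
- Probability of a no-difference verdict: 1 − π.
- Probability that the rule is met: π(d_diet, n) × [1 − π(d_control, n)].
- Between-arm test of change: noncentral t with 2n − 2 degrees of freedom and noncentrality (d_diet − d_control)√(n/2).

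**Step 1: how often a real control-arm shift is called no difference.** For example, d = 0.3 and n = 23 give noncentrality 0.3 × √23 = 1.44, π = 0.280 and 1 − π = 0.720.

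| True control shift d | n = 23 | n = 46 |
|---|---|---|
| 0.2 | 85% | 74% |
| 0.3 | 72% | 49% |
| 0.4 | 55% | 24% |
| 0.5 | 37% | 9% |

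**Step 2: both sides change equally, so the diets did not separate.** For example, d = 0.4 and n = 23 give 0.450 × 0.550 = 0.248.

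| Common d | Rule met, n = 23 | Rule met, n = 46 |
|---|---|---|
| 0.3 | 20% | 25% |
| 0.4 | 25% | 18% |
| 0.5 | 23% | 8% |

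A between-arm test errs 5% of the time here by construction. Simulation with 50,000 runs gave 4.9% (n = 23, d = 0.4) and 5.0% (n = 46, d = 0.3), with the rule met in 24.7% and 25.2% of runs.

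**Step 3: the diet side changes twice as much as the control side.**

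| d diet vs control | n per side | Rule met | Between-arm power |
|---|---|---|---|
| 0.8 vs 0.4 | 23 | 53% | 26% |
| 0.8 vs 0.4 | 46 | 24% | 47% |
| 0.8 vs 0.4 | 92 | 3% | 77% |
| 1.2 vs 0.6 | 46 | 2% | 81% |

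Where control arms drift at all, more data make the rule less likely to recognise a true separation, while the direct comparison improves.

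**Step 4: the stricter reading.** The text does not say whether arms are pooled. If both diet arms of 23 must be significant and both non-diet arms non-significant, the equal-change pass rate falls: π²(1 − π)² = 4% to 6% for d = 0.3 to 0.5. The cost is recognition of a true separation: for 0.8 vs 0.4 the rule is met in 28% of trials, and for 1.2 vs 0.6 in 5%. A between-arm test on the same patients (46 per side) has 47% and 81% power. Even with no control change at all, the non-diet half then fails in 1 − 0.95² = 9.75% of trials.

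**The case against.** The strongest reply is that DQ carries little weight. It sits under quality control and compliance and is neither the primary nor a listed secondary outcome. No efficacy analysis, exclusion or conclusion is tied to it, and the study is exploratory. That stands, and it limits the severity.

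Four stronger readings are tempting, and the document does not support them.

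- *That this is the only check on diet delivery, so a null diet result could not be interpreted.* DCR is defined in the same section, and intake frequencies and qualified meals are also calculated from the diary. They remain available whatever the DQ label says.
- *That failing the rule would fail the trial.* Nothing in the protocol follows from failing it.
- *That before and after values come from different instruments.* A reader might infer that the before value is the past-year dietary history and the after value the 28-day diary. The protocol does not say so, and Supplementary Table 3 is not shown. The point is conditional: if it is so, a shift due to the instrument would act on each within-group test but would largely cancel between randomised arms.
- *That an unpaired test is planned for paired data.* The sentence in 2.15 can be read as a comparison of arms, for which chi-square or Fisher suits independent groups.

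That last reading does not rescue the criterion. Section 2.12.5 still defines high diet quality by the two within-group verdicts, and 2.15 does not replace that definition. Nor is this detail left to an analysis plan: the rule is stated, and an analysis plan would have to overturn it.

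**Conclusion.** The point holds as a minor one. As worded, the criterion can call the diets separated when they are not, and can miss a separation that is real. The size depends on assumed effects and on whether arms are pooled. The false-pass rate under equal change ranges from about 4% to 6% (all four arms of 23 judged separately) to about 20% to 25% (one arm against one, n=23), for shifts of 0.3 to 0.5 SD. A control shift of 0.2 to 0.5 SD goes unrecognised in 85% to 37% of trials at n=23 and in 74% to 9% at n=46. The percentages rest on a paired t-test stand-in. The fault in the logic does not depend on them, because no part of the rule estimates the difference between arms. The consequence is confined to judging whether the diet contrast was delivered; the efficacy tests are untouched.

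**What to change.** In 2.12.5 and 2.15, replace the rule with a diet versus non-diet comparison of each patient's post-treatment intake frequency of the LVD foods, adjusted for baseline intake, reported as a difference with a 95% confidence interval. State the direction that counts as movement toward the diet. Name the source of the baseline value; used as a covariate, it need not come from the same instrument as the later value.

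Also compare the share of qualified meals from the diary across all four arms, and report the value in the non-diet arms as contamination rather than compliance. If a chi-square or Fisher test is kept for any diet indicator, say that it compares arms.

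The cost is wording and slightly more analysis work. The diary is already required of patients in all four arms and DQ is already assessed at baseline, so no new data are needed. What is lost is the single pass/fail label.

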Prolonged colonic transit time (slow transit constipation, STC), pelvic floor muscles dysfunction (functional defecation disorder) and their combined effects are the well-established mechanisms involved in the development of FC. The latest diagnosis of FC is based on the criteria of Rome IV Standard, including laborious defecation, dry or lumpy stool, incomplete defecation, anorectal obstruction, prolonged defecation cycle, and manually assisted defecation. Two or more of the above items need to be included with at least 25% frequency for each one. Meanwhile, loose stool is rarely present without laxative and irritable bowel syndrome (IBS) should be excluded.^[7]^ Dry or lumpy stool is not necessary for FC diagnosis as many patients whose stool is not that dry or lumpy but sticky, complain of difficult defecation. However, there are few studies on this kind of constipation. In TCM, gastrointestinal damp-heat syndrome is the major FC syndrome that accounts for almost 32.5% FC cases.^[8]^ Heat evil results in formation of dry or lumpy stool, which is in agreement with typical understanding of FC in western medicine, while damp evil inclines to cause sticky stool in TCM theory. Based on that, the classification therapy shows greater therapeutic efficacy against FC with gastrointestinal damp-heat syndrome. Thus, we can divide this FC syndrome into 2 subtypes that are heat more than damp syndrome (typical functional constipation, TFC) and damp more than heat syndrome (atypical functional constipation, aTFC). Drugs therapy is still the main method for effective FC treatment. For TFC, Macrogol 4000 Powder is one of the effective and safe drugs, which can increase the average number of defecation per week by 1.9 times as compared to placebo.^[9]^ On other hand, the effectiveness of Chinese herb for aTFC could reach 66.7% to 72.7%.^[10]^ However, it has been recently reported that only 25.1% among 6318 Chinese adults with constipation selected laxatives, while 81.7% of them preferred lifestyle and dietary changes as treatment option.^[11]^ The results of a current study have shown a close relationship between the intestinal flora and FC,^[12]^ but their causal relationship still remains unclear.^[13]^ Different eating habits such as low intake of water, fruits and vegetables and high intake of spicy, greasy food all contribute to the increased prevalence of FC.^[14]^ Similarly, increased intake of whole fruits, especially fruit fiber can protect colonic gastrointestinal health.^[15]^ Additionally, another report indicated that five days of dietary changes could quickly alter the human intestinal flora.^[16]^ Therefore, the correlation between diet and constipation may be explained by changing the intestinal flora.

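### Section 2.12.5 defines high diet quality by two within-group significance verdicts, so it neither contrasts diet with non-diet patients nor shows that non-diet patients kept their diet

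*Protocol article*

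**What the plan says.** All references are to the protocol article.

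- Section 2.12.5 (DQ and compliance measure) gives the definition: "Diet high quality means a significant difference before and after intervention in diet groups, while there is no difference in non-diet groups". The same section also defines a dietary compliance rate, the percentage of meals that qualify, and calls compliance high from 80% upwards.
- Section 2.11 (Quality control) gives the timing: "DQ will be assessed at the baseline and after the intervention".
- Section 2.8 (Interventions) says what the comparison groups are to do: "patients without diet intervention will continue their previous eating habits".
- Section 2.15 (Planned statistical analysis) names the tests: "Safety, dietary quality, compliance indicators will be tested by chi-square test or Fisher exact test". Its only criterion for significance is that a P "value <.05 will be considered statistically significant".
- Sections 2.2 and 2.6 fix the numbers. Within each subtype patients go to "drug + diet group, placebo + diet group, drug group and placebo group randomly at 1:1:1:1 ratio", with "23 participants in every sub-group".

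**The concern.** The rule is meant to show that the two dietary regimens differed as intended. It has two faults.

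1. A significant change in one group and a non-significant change in another do not show that the two changes differ. That needs a direct comparison of the changes. The trial is randomised, so the comparison is available, but the definition does not use it.
2. A non-significant change in 23 or 46 patients does not show that these patients ate as before. Neither section 2.12.5 nor section 2.15 gives a margin or an interval, so the part of the rule that concerns non-diet patients can only mean P ≥ .05. A small or noisy sample then counts as evidence of stability.

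Patients know their diet allocation (section 2.9), and all are asked to keep a food diary (section 2.8). A shift in reported diet that is common to all arms is therefore possible. Such a shift cancels in a between-arm comparison of change and does not cancel under this rule. At stake is whether the report can say credibly that the diet and non-diet groups ate differently.

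**Working it through.** **Inputs.** The documents give no effect size, SD, margin or power for diet quality, so there is no planned figure to reproduce. The group sizes follow from sections 2.2 and 2.6: 92 / 4 = 23 per arm, and 2 × 23 = 46 diet against 46 non-diet patients within a subtype. Alpha is .05 (section 2.15); two-sided is assumed.

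**Further assumptions.** There is one diet score, analysed by a paired t-test, with the same SD of change in every arm. The true mean change d, in units of that SD, is varied from 0.2 to 0.5.

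**Formulas.**

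- p is the power of the paired t-test with n patients: the probability that a noncentral t variable (n − 1 degrees of freedom, noncentrality d√n) falls outside ± the 97.5% point of the central t.
- A real change d in non-diet patients is read as no difference with probability 1 − p.
- If diet and non-diet patients change by the same d, one diet group against one non-diet group meets the rule with probability p(1 − p).
- If both diet arms must be significant and both non-diet arms not, the probability is p²(1 − p)².

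**Results** (products taken from unrounded values).

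| d | p, n=46 | 1 − p | p(1 − p) | p, n=23 | 1 − p | p(1 − p) | p²(1 − p)², four arms of 23 |
|---|---|---|---|---|---|---|---|
| 0.2 | 0.264 | 0.736 | 0.194 | 0.151 | 0.849 | 0.128 | 0.016 |
| 0.3 | 0.512 | 0.488 | 0.250 | 0.280 | 0.720 | 0.202 | 0.041 |
| 0.4 | 0.756 | 0.244 | 0.184 | 0.450 | 0.550 | 0.248 | 0.061 |
| 0.5 | 0.913 | 0.087 | 0.080 | 0.630 | 0.370 | 0.233 | 0.054 |

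When both groups change equally, a direct two-sided 5% test of the difference in change is significant in 5% of trials by construction, and in favour of diet in 2.5%.

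**Real separation with some drift.** Suppose diet patients change by 0.8 SD and non-diet patients by 0.4 SD.

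- 23 v 23: the rule is met with probability 0.956 × 0.550 = 0.526. The direct test has power 0.273.
- 46 v 46: the rule is met with probability 1.000 × 0.244 = 0.244. The direct test has power 0.483.

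Doubling the number of patients makes the direct test more likely to find the real difference and makes the rule less likely to be met. A larger sample detects the control drift, and the rule then withholds the label although the groups differ.

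**The case against.** Much can be said on the other side, and several stronger readings that a reader might infer fail.

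- **That this is the trial's only check on the diet.** It is not. The compliance rate in section 2.12.5 is a second fidelity measure and uses no P value. It measures adherence to the diet, however, and does not test separation between arms.
- **That the protocol never compares the groups on diet.** This cannot be said of the whole document. The tests named in section 2.15 are for independent samples, and dietary quality is listed there beside safety, so a between-group comparison may be meant. But the sentence states no contrast and does not alter the definition in 2.12.5.
- **That the reading of the primary outcome, bowel movements per week, depends on the label.** Nothing makes that analysis, its population or its conclusion depend on diet quality.
- **That contamination of the non-diet arms is likely.** The introduction reports that, of Chinese adults with constipation, "81.7% of them preferred lifestyle and dietary changes as treatment option". That is a preference in a cited survey, not behaviour of trial controls, who are told to keep their habits. Open allocation makes contamination possible; its likelihood is not shown.
- **That the rule certifies a failed contrast in a quarter of trials.** The value 0.25 is the mathematical ceiling of p(1 − p), and 0.3 SD at n=46 happens to reach it. The range must be shown, and the figure is far lower if the four arms are judged separately.
- **That testing many foods would almost guarantee a false difference.** A figure such as 1 − 0.95^20 = 0.64 supposes ten foods tested independently in two arms. The document states neither the number nor the independence.

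It is also fair to object that the document does not name the paired t-test for diet quality and that the trial calls itself exploratory. Both points limit the size and severity of the finding. The fault in the definition remains.

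**Conclusion.** The point holds for the definition in section 2.12.5. It is a stated decision rule, not a detail left to another document, and it is wrong as written: it omits the contrast between diet and non-diet patients and takes non-significance as absence of change.

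Under the assumptions given, and for changes of 0.2 to 0.5 SD:

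- A real drift in non-diet patients passes as no difference in 74% down to 9% of trials (n=46) or 85% down to 37% (n=23).
- With equal change in both groups the rule still declares high quality in 8–25% (46 v 46) or 13–25% (23 v 23). If all four arms of 23 must comply, this is 2–6%, about 4% at 0.3 SD. The comparator is 2.5% favouring diet for a direct test.

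The text does not say whether arms are pooled or judged one by one. The logical fault is the same either way; only its size differs. Because it concerns a fidelity measure in an exploratory trial and not the primary outcome, severity is minor to moderate.

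**What to change.** Replace the definition in section 2.12.5, and name the matching analysis in section 2.15, along these lines:

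> Diet separation is the difference between diet and non-diet patients (diet minus non-diet, within each subtype) in the before-after change of one pre-stated diet measure, obtained in the same way at baseline and after the intervention, with its 95% confidence interval. The mean change in the non-diet arms is reported with its 95% confidence interval. A non-significant change is not taken as absence of change.

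The compliance rate can stay as it is, as a separate measure.

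The cost is a rewording of two sections, with no additional patients. One point needs checking first. Section 2.12.1 records baseline diet as habits over the past year, while the diary in section 2.8 covers the treatment period. The baseline questionnaire (Supplementary Table 3) is not shown, so it cannot be confirmed here that the planned data already yield one comparable before-after measure. If they do not, the same instrument has to be used at both times.
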